## Abstract

**Introduction:**

Continuous progress in atrial fibrillation (AF) ablation techniques has led to an increasing number of procedures with improved outcome. However, about 30–50% of patients still experience recurrences within 1 year after their ablation. Comprehensive translational research approaches integrated in clinical care pathways may improve our understanding of the complex pathophysiology of AF and improve patient selection for AF ablation.

**Objectives:**

Within the “IntenSive mOlecular and eLectropathological chAracterization of patienTs undergoIng atrial fibrillatiOn ablatioN” (ISOLATION) study, we aim to identify predictors of successful AF ablation in the following domains: (1) clinical factors, (2) AF patterns, (3) anatomical characteristics, (4) electrophysiological characteristics, (5) circulating biomarkers, and (6) genetic background. Herein, the design of the ISOLATION study and the integration of all study procedures into a standardized pathway for patients undergoing AF ablation are described.

**Methods:**

ISOLATION (NCT04342312) is a two-center prospective cohort study including 650 patients undergoing AF ablation. Clinical characteristics and routine clinical test results will be collected, as well as results from the following additional diagnostics: determination of body composition, pre-procedural rhythm monitoring, extended surface electrocardiogram, biomarker testing, genetic analysis, and questionnaires. A multimodality model including a combination of established predictors and novel techniques will be developed to predict ablation success.

**Discussion:**

In this study, several domains will be examined to identify predictors of successful AF ablation. The results may be used to improve patient selection for invasive AF management and to tailor treatment decisions to individual patients.

## Introduction

The prevalence of atrial fibrillation (AF) has risen substantially over the past decade, and it continues to rise due to the aging population and the increasing rate of concomitant risk factors and underlying structural heart diseases (1). AF is associated with an increased risk of ischemic stroke, developing and worsening of heart failure, and a significant symptom and financial burden (2). To maintain sinus rhythm and to decrease symptoms related to AF, catheter ablation is recommended in symptomatic patients (3). However, despite advanced ablation techniques and improved ablation outcomes over the last decade, about 30–50% of patients still experience recurrences of atrial arrhythmias within 1 year after the procedure (4, 5).

Although several readily available characteristics (including demographic information, established clinical AF risk factors, and left atrial volume) have previously been identified as predictors for AF ablation success, it remains challenging to estimate the success rate for an individual patient (6). A range of novel techniques estimating the extent of the atrial AF substrate has been proposed: to aid in the prediction of individual success rates biomarkers, such as inflammatory mediators and markers for fibrosis (7, 8), common gene variants associated with AF, and non-invasive electrophysiological characteristics recorded on surface electrocardiograms (ECG) (9, 10). Additionally, a more detailed characterization of different AF patterns based on frequency, duration, and manner of conversion of AF episodes might further help to characterize the AF phenotype, although its predictive value for ablation success has not yet been described (11).

It is the aim of the multicenter prospective “IntenSive mOlecular and eLectropathological chAracterization of patienTs undergoIng atrial fibrillatiOn ablatioN (ISOLATION)” cohort study to systematically examine predictors of successful AF ablation in the following domains: (1) clinical factors, (2) AF patterns detected using rhythm monitoring devices, (3) anatomical characteristics, (4) electrophysiological characteristics, (5) circulating biomarkers, and (6) individual genetic background. Factors from these domains will be combined in a multimodality model for the prediction of ablation success, which may help to improve patient selection for invasive AF management. Herein, we outline the design of the ISOLATION study and describe how all study procedures are implemented into a standardized, integrated clinical care and research AF ablation pathway.

## Methods and Analysis

### Study Design

The ISOLATION is a multicenter prospective cohort study designed to identify predictors of successful AF ablation in six different domains (Figure 1). The study was initiated in July 2020 and aims to include 650 patients scheduled for AF ablation in two Dutch university hospitals, the Maastricht University Medical Centre (MUMC) and the Radboud University Medical Centre (Radboudumc). Clinical characteristics, results of routine clinical tests (e.g., laboratory results, cardiovascular imaging) and several additional study procedures are collected before, during, and after the ablation. The study protocol was reviewed and approved by the ethics committee of the MUMC (METC azM/UM, NL70787.068.19) and is registered at clinicaltrials.gov (NCT04342312) and in the Netherlands Trial Register (NL7894).

**FIGURE 1 F1:**
[figure not shown]
The 6 domains of interest in which predictors for successful atrial fibrillation ablation are sought: (1) clinical risk factors, (2) pre-procedural AF patterns, (3) anatomical characteristics, (4) electrophysiological characteristics, (5) circulating biomarkers, and (6) genetic background. AF, atrial fibrillation; CT, computed tomography; ECG, electrocardiogram; MRI, magnetic resonance imaging. Study procedures with an asterisk are conducted for a subset of patients.

### Study Population

Patients are eligible for participation in this study if they are 18 years of age or older, have documented AF, are scheduled for an AF ablation (first procedure or redo) in either participating center, and are able and willing to provide written informed consent. There are no restrictions for AF ablation modality nor for potential previous ablation procedures. Possible ablation modalities include percutaneous techniques (cryoballoon ablation or radiofrequency ablation), surgical ablations (epicardial ablation, concomitant ablation) or a combined procedure (hybrid ablation). Patients are excluded if they are deemed unfit to participate due to a serious medical condition or if they undergo an emergency procedure. In- and exclusion criteria are listed in Table 1.

**TABLE 1 T1:** In- and exclusion criteria of the ISOLATION study.

**Inclusion criteria**	
1	18 years of age or older;
2	Documented atrial fibrillation;
3	Scheduled for atrial fibrillation ablation or redo atrial fibrillation ablation;
4	Able and willing to provide written informed consent.
**Exclusion criteria**	
1	Patients deemed unfit to participate due to a serious medical condition before ablation, as deemed by their treating physician;
2	Patients undergoing an emergency ablation procedure.

### Endpoints

The primary outcome measure is ablation success, defined as freedom from documented recurrence of atrial arrhythmia 12 months after the index procedure. Recurrences in the first 3 months are exempted (blanking period). Atrial arrhythmias are defined as AF, atrial tachycardia, or non-isthmus dependent atrial flutter. Episodes of atrial arrhythmia must be documented on an ECG, Holter monitoring (minimum duration of 30 seconds), or an implanted device (atrial high rate episode during at least 5 minutes or mode switch, confirmed as being AF or other atrial arrhythmia by a trained physician). To detect symptomatic and asymptomatic recurrences of atrial arrhythmias, 48-h Holter monitoring is performed at 6 and 12 months after the ablation procedure. Holter recordings may be extended or additional Holter recordings may be added when clinically indicated. 12-lead ECGs are obtained at 3 and 12 months, and patients are encouraged to have additional ECGs recorded if they experience symptoms between visits.

Key secondary outcomes include time to first recurrence of atrial arrhythmia or AF after the blanking period, freedom from documented recurrence of atrial arrhythmia at 24 months, redo procedures, disease progression to persistent or permanent AF, changes in circulating biomarkers, and changes in non-invasive electrophysiological markers for substrate quantification (Table 2).

**TABLE 2 T2:** Primary and secondary endpoints in the ISOLATION study.

Primary endpoint
Ablation success, defined as freedom from documented recurrence of atrial arrhythmia after 12 months. Recurrences in the first 3 months after the index procedure (blanking period) are exempted.

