### Post-ablation Follow-Up

After the ablation procedure, patients return to the outpatient clinic at 3 and 12 months and have scheduled teleconsultations after 6 and 24 months. Prior to the contacts at 6, 12, and 24 months, a 48-h Holter recording is performed. 12-lead ECGs are obtained during every on-site follow-up visit. In addition, patients receive an on-demand 7-day prescription for the use of the smartphone application FibriCheck (Qompium, Hasselt, Belgium) prior to all scheduled consultations. FibriCheck is an app that uses photoplethysmogram (PPG) signals to assess heart rate regularity and symptom-rhythm correlation (13). Patients are instructed to measure 3 times per day and in the case of symptoms, in accordance with the TeleCheck-AF approach (14). If irregularity of the heartbeat is detected and AF is suspected, additional or longer Holter recordings may be performed to confirm AF recurrence by ECG documentation (Figure 3B, standard follow-up procedures in white).

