### Limitations

The ISOLATION study and ISOLATION “light” registry have several limitations. First, the type of AF ablation that is performed is not standardized but is decided upon by a patients’ treating physician. Success rates of different strategies vary and this may impact the rate in which the primary endpoint occurs. Second, monitoring for recurrences of atrial arrhythmia is performed intermittently using ECGs, Holter recordings, and PPG-based monitoring, but lack of continuous rhythm monitoring may lead to an underestimation of the number of endpoints (18). Third, only AF patients scheduled for AF ablation are included. Results found in this cohort may not be generalizable to the entire AF population. Fourth, not all patients undergoing AF ablation will agree to study participation. Although the integration with the ISOLATION “light” registry helps to include nearly all patients undergoing AF ablation, the specific study procedures are only conducted for participants in the main ISOLATION study. Fifth, the study reflects a large, real-world cohort of AF ablation patients. Due to the world-wide COVID-19 pandemic and to incident logistical reasons, protocol deviations may occur (e.g., a longer than desirable waiting time for ablation or out-of-window follow-up visits).

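### Recurrence is detected more readily in some patients than in others, so traits linked to closer monitoring could be selected as predictors, and no analysis restricted to scheduled recordings is named

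*Protocol article*

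**What the plan says.** The Endpoints section defines the primary outcome by documentation: "The primary outcome measure is ablation success, defined as freedom from documented recurrence of atrial arrhythmia 12 months after the index procedure". A 3-month blanking period is left out of the count.

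A common minimum applies to everyone: "48-h Holter monitoring is performed at 6 and 12 months after the ablation procedure" and "12-lead ECGs are obtained at 3 and 12 months". Post-ablation Follow-Up adds an on-demand 7-day prescription for a smartphone pulse app before each scheduled consultation. The app is not itself a qualifying source, because a suspected recurrence must be confirmed by ECG.

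Four further routes can supply or trigger a qualifying event, and they are not equal across patients:

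- Devices: an event may come from "an implanted device (atrial high rate episode during at least 5 minutes or mode switch", with confirmation by a trained physician.
- Symptoms: "patients are encouraged to have additional ECGs recorded if they experience symptoms between visits".
- Clinical judgement: "Holter recordings may be extended or additional Holter recordings may be added when clinically indicated".
- App findings: "If irregularity of the heartbeat is detected and AF is suspected, additional or longer Holter recordings may be performed to confirm AF recurrence".

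The section on the prediction model and sample size takes the three variables most strongly correlated with ablation success from each of domains 1 to 5, the two strongest from domain 6, and ablation technique. Logistic regression then uses forward selection with AIC. The sensitivity analysis named there repeats the performance assessment by ablation strategy. On detection, the Limitations section says that "lack of continuous rhythm monitoring may lead to an underestimation of the number of endpoints".

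**The concern.** Whether a patient is recorded as a failure depends on two things: whether the arrhythmia recurred, and how closely the patient was observed. If the second were the same for everyone, the main harm would be fewer events and weaker associations. Here it varies with device carriage, symptoms and clinical judgement. These may plausibly go with candidate predictors such as age, comorbidities and pre-procedural AF pattern, although the article gives no data on this.

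The aim of the study is to find predictors. Neither the ranking within domains nor the forward selection can separate a correlation with recurrence from a correlation with detection. A trait that brings closer monitoring can look harmful. A trait that truly worsens outcome but goes with lighter monitoring can be lost. Discrimination measured against the same recorded outcome would not show either error.

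**Working it through.** **The plan's own figures.** Candidate variables: 5 × 3 + 2 + 1 = 18. Events at 10 per variable: 180. Patients: 180 / 0.32 = 562.5, so 563, as stated. With 650 enrolled and 15% lost, 650 × 0.85 = 552.5 are evaluable, and 552.5 × 0.32 = 176.8 events are expected. These figures only set the scale for what follows.

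**What the article does not give.** It reports no device prevalence, no detection sensitivity by route and no frequency of extra recordings. The bias cannot be computed; it can only be illustrated.

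**Assumptions.**

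- True recurrence 45% in everyone. This lies inside the 30–50% range that the Introduction gives for recurrence within 1 year.
- Detection 95% with a device, and 60% (range 50–70%) without.
- A binary trait with no effect on recurrence, whose carriers have a device in 30% of cases, against 5% of non-carriers.

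**Recorded recurrence by device status** = true recurrence × detection.

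- Device: 0.45 × 0.95 = 0.4275.
- No device: 0.45 × 0.60 = 0.270 (0.225 at 50%, 0.315 at 70%).
- Odds ratio: (0.4275/0.5725) / (0.270/0.730) = 2.02 (2.57 at 50%, 1.62 at 70%).

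This compares device carriers with non-carriers. The article does not name device carriage as a candidate predictor, so the trait is the relevant case.

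**Recorded recurrence by trait**, weighting the two rates by device carriage.

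- With trait: 0.30 × 0.4275 + 0.70 × 0.270 = 0.317.
- Without trait: 0.05 × 0.4275 + 0.95 × 0.270 = 0.278.
- Odds ratio: (0.317/0.683) / (0.278/0.722) = 1.21.
- At 50% detection without a device: 0.286 versus 0.235, odds ratio 1.30.
- At 70%: 0.349 versus 0.321, odds ratio 1.13.

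**Same calculation with the plan's 32% taken as true recurrence.** Device 0.304; no device 0.160, 0.192 and 0.224 at 50%, 60% and 70%.

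- At 50%: 0.203 versus 0.167, odds ratio 1.27.
- At 60%: 0.226 versus 0.198, odds ratio 1.18.
- At 70%: 0.248 versus 0.228, odds ratio 1.12.

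The range of about 1.1 to 1.3 therefore does not hinge on the 45%.

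**Against sampling error.** Suppose half of 552 patients carry the trait (276 per group; assumption). In the central 45% case the standard error of the difference is √(0.317 × 0.683/276 + 0.278 × 0.722/276) = 0.039. The spurious difference is also 0.039, about one standard error. That would seldom reach significance alone, but it can change the order of weak candidates, and order decides which three enter from a domain.

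**A trait that marks close monitoring perfectly** (upper bound). With 32% true recurrence, 552 patients, and 10–50% of them closely monitored:

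| Detection, close vs other | Recorded recurrence | Odds ratio | Chance of p < 0.05 |
|---|---|---|---|
| 100% vs 90% | 32.0% vs 28.8% | 1.16 | 8–13% |
| 95% vs 80% | 30.4% vs 25.6% | 1.27 | 13–24% |
| 95% vs 70% | 30.4% vs 22.4% | 1.51 | 28–57% |
| 95% vs 60% | 30.4% vs 19.2% | 1.84 | 50–86% |

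Real candidates would mark monitoring only in part, so they would fall below these rows.

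**The case against.** The strongest reply is that the gap in monitoring may be small. Everyone has the scheduled ECGs and Holters and is offered the app. It would be wrong to read the plan as leaving patients without a device only two 48-hour windows. The device criterion is also stricter: at least 5 minutes or a mode switch, with physician confirmation, against 30 seconds on Holter. Both points narrow the contrast, and 95% versus 60% may be too wide. They do not remove it, because app use is on demand, confirmation is discretionary, and the other extra routes follow symptoms and clinical judgement.

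A second reply is that under-detection is disclosed, the model is called exploratory, and further sensitivity analyses usually belong in an analysis plan. The disclosure is real, but it covers the number of endpoints and not a difference between patients, which is what threatens a search for predictors. The exploratory label limits the claims made; it does not stop a detection-driven variable from being selected.

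A reader might also infer that patients who miss their Holters are counted as successes, since success is the absence of a documented recurrence. The article does not say so. It does not discuss missed Holters, it allows for 15% loss to follow-up and plans multiple imputation, and rules on when an outcome can be assessed may stand in the full protocol or analysis plan. That inference is not supported and forms no part of this point.

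**Conclusion.** The concern holds in limited form. Opportunity for detection differs between patients by design, predictors are chosen by correlation with the recorded outcome, and the article neither acknowledges differential detection nor names an analysis that would show it. Following the plan as written could select variables that predict being observed.

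The size is unknown. Under the stated assumptions on recurrence, detection and device carriage, a trait with no effect gets an odds ratio of about 1.1 to 1.3. A reader might take the odds ratio of 2.0 for device carriers as the likely bias in a predictor; it is not, because an ordinary trait shares only part of that contrast. The illustration shows that the bias can matter for selection. It does not show that it will be present.

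**What to change.** Before outcomes are analysed, pre-specify two sensitivity analyses and one change of wording.

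1. Refit the model with the outcome based only on the scheduled ECGs and Holters, ignoring events known solely from a device or from triggered recordings. Where a scheduled Holter was extended, use its first 48 hours.
2. Refit the model on the planned outcome with implanted-device status included as a covariate.
3. Flag any predictor that does not persist in both, and extend the Limitations text to say that detection may differ between patients and may be related to candidate predictors.

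The cost is wording and two refits, provided that device status and the source of each recording are available in the collected data, which the article does not confirm. The scheduled-only analysis has fewer events. If 10–20% of the expected 176.8 came only from unscheduled sources (assumption), 176.8 × 0.9 = 159 to 176.8 × 0.8 = 141 would remain, or 8.8 to 7.9 per variable. It can also miss recurrences that were treated before a scheduled recording, and it equalises the opportunity for detection, not the chance that a short episode falls inside a recording. It therefore belongs beside the primary analysis, not in its place.

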**Secondary endpoints**
Time to recurrence of atrial arrhythmia after the blanking period;
Time to recurrence of AF after the blanking period;
Freedom from documented recurrence of atrial arrhythmia after 24 months. Recurrences in the blanking period are exempted;
Early AF recurrences, defined as any episode of AF during the blanking period;
Early recurrences of atrial arrhythmia, defined as any episode of AF, atrial tachycardia or non-isthmus dependent atrial flutter during the blanking period;
Disease progression to persistent or permanent AF;
Changes in circulating biomarkers and non-invasive electrophysiological markers for substrate quantification;
Use of antiarrhythmic drugs 1 year after ablation;
Redo procedures, defined as repeated ablation procedure with the goal to prevent recurrence of AF or reduce the AF burden after one or more previous attempts to achieve the same goal;
Number of veins with pulmonary vein reconnection at redo procedure;
Major adverse cardiovascular events.

### Study Enrollment

Patients accepted for AF ablation receive verbal and written information about the ISOLATION study and are scheduled to visit a standardized AF ablation work-up pathway. Patients willing to participate provide written informed consent for ISOLATION prior to their visit at the work-up pathway, or during this pathway but prior to all study procedures. Patients that decline participation in the ISOLATION study are asked to participate in the “light” version of the study, the “Clinical electrophysiology registry MUMC + and Radboudumc” (ethical committee number 2019–1022). Participants in this ISOLATION “light” registry undergo the same standardized pre- and post AF ablation pathway, with the exception that most of the study procedures are omitted. Patients that do not wish to participate in either study complete the standardized pathway without any additional study procedures (Figure 2).

**FIGURE 2 F2:**
[figure not shown]
Flowchart of the standardized, integrated clinical care and research pre- and post AF ablation pathway. Structure of the pre- and post AF ablation pathway and general recommendations for the type of AF ablation. Treating physicians may choose to deviate from these recommendations depending on specific patient characteristics of patient preference. *Thoracocopic/hybrid ablation is strongly considered if LAVi >5− ml/m^2^ or in case of patient preference. AF, atrial fibrillation; LAVi, left atrial volume index; RF, radiofrequency.

### Pre-ablation Work-Up

The standard work-up for ablation in the participating centers consists of a systematic collection of clinical information, vital signs, 12-lead ECG, blood tests, imaging to assess pulmonary vein anatomy (either computed tomography or cardiac magnetic resonance imaging), and screening by an anesthesiologist. Echocardiography is performed in patients without recent imaging or when recent imaging is of insufficient quality. During the work-up, patients are systematically screened for common comorbidities and triggers for AF such as hypertension, obesity, hyperlipidemia, diabetes mellitus, and chronic obstructive pulmonary disease (COPD) according to current AF guidelines (3). In addition, all patients without known obstructive sleep apnea (OSA) are referred for remote testing for sleep disordered breathing, as described previously in more detail (12). If any of the risk factors is present, applicable treatment is initiated parallel to the AF treatment.

The pre-ablation preparation is structured in a care pathway at the outpatient clinic that allows the entire work-up to be completed in a single visit (Figure 3A, standard work-up procedures in white). All patients scheduled for AF ablation complete this pre-AF ablation work-up, regardless of study participation.

